# Protocol for a randomized controlled dismantling study of a brief telephonic psychological intervention applied to non-professional caregivers with symptoms of depression

**DOI:** 10.1186/s12888-015-0682-8

**Published:** 2015-11-23

**Keywords:** Non-professional caregiver, Indicated prevention, Depression, Telephone intervention, Dismantling strategy, Study protocol

## Abstract

**Background:**

Although depression is a common problem in caregivers and there are effective cognitive-behavioral interventions for its prevention, the ability of caregivers to attend these treatments is often limited by logistics. Furthermore, the efficacy of the components of these interventions is unknown. The objectives of this study are to (a) evaluate the efficacy of a telephone-administered cognitive-behavioral intervention to prevent depression with all its components (cognitive and behavioral) and only with behavioral activation, and to (b) analyze the mediators of the change in depressive symptoms.

**Methods/Design:**

A randomized controlled clinical trial was designed to dismantle the components of a cognitive-behavioral intervention. Caregivers with elevated depressive symptoms will be randomly assigned to a cognitive-behavioral intervention, an intervention with only the behavioral activation component, or a usual care control group. Each condition will consist of approximately 60 participants. The two interventions will consist of five sessions lasting 90 min each, applied to groups of about 5 participants at a time via conference call. Trained interviewers, blind to the experimental conditions, will conduct the assessments at the pre-treatment, post-treatment and 1-, 3-, 6- and 12-month follow-ups.

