### Sample size

Based on previous studies of indicated prevention of depression in caregivers [10, 11, unpublished paper of Note 1] and studies that have administered therapies for depression by phone (see [13]), we estimate that a sample size of 56 participants per group (168 in total) will be sufficient to detect a difference of 19 % in the rates of incidence of depression episodes between experimental and control conditions, assuming α = .05 and a power (1 - β) of .80. However, assuming an attrition rate of 5-8 %, we estimate that the sample size for each of the groups should be approximately 60 subjects (180 in total).

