### Randomization

Those subjects who meet the eligibility criteria and have signed the informed consent forms will be randomly assigned to the CBC, BAC or CG groups by an external statistician using a table of random numbers. The scrambling sequence will be communicated to researchers through numbered sealed envelopes, one for each participant, with instructions to use them in numerical order.

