### Interventions

The manuals for the intervention protocols will be developed during the first months of the project. Psychologists who have been trained by two experienced clinicians, each with over 20 years experience in cognitive-behavioral therapies, will administer the interventions. Therapists will receive about 35 h of training consisting of theoretical and practical seminars and role-playing exercises. They will administer the interventions following the treatment manuals and will be monitored weekly. Each intervention will be administered via conference call and will consist of five 90-min group sessions once a week. All sessions will be recorded and the clinicians involved in the training of therapists will use the recordings to assess adherence to established protocols.

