#### Usual Care Control Group (CG)

Usual care will constitute the control condition. People assigned to this group will receive no intervention or psychoeducational material. However, we will offer them the possibility of accessing any medical or psychological treatment (public or private) available in their community to treat depressive symptoms.

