### Statistical analyses

All analyzes will be conducted in accordance with the principle of intention to treat. All participants will be analyzed in the group to which they were assigned. The most conservative approach for attrition will be adopted by considering dropouts as a treatment failure (i.e., a major depressive episode was triggered) and by replacing missing data with the corresponding baseline scores. Cumulative incidence rates of depression for all three groups will be calculated to examine the efficacy of the interventions on prevention of major depressive episodes. The relative risk (RR) and number needed to treat (NNT) will be calculated according to the formulas proposed by Guyatt et al. [38]. Also, the time it takes for the participants to suffer a major depressive episode will be analyzed using a survival analysis. The effect of the interventions on depressive symptoms will be examined by using mixed factorial analysis of variance (ANOVA) tests with repeated measures. To examine the relationship of the received interventions and depressive symptoms as mediated by change in automatic negative thoughts, self-efficacy, and reinforcement, we will utilize the method recommended by Baron and Kenny [39]. The acceptability and adherence to interventions will be examined by using the Chi-Square test to compare the percentages of dropouts and the Student *t*-test for independent samples will be used to compare session attendance and homework completion. The level of participant satisfaction with the interventions will be analyzed with frequency distribution of each item in the CSQ-8, and we will compare results across both conditions using the Student *t*-test for independent samples. All analyzes will be conducted using SPSS for Windows, version 20.0.

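### CBC and BAC are delivered in call groups of about five, but the sample size and the tests the protocol names make no allowance for correlation within those groups

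*Protocol article*

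**What the plan says.** The Abstract (Methods/Design) states that both interventions are "applied to groups of about 5 participants at a time via conference call". The Interventions section confirms the format: "Each intervention will be administered via conference call and will consist of five 90-min group sessions once a week".

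Allocation is individual. The Randomization section uses "numbered sealed envelopes, one for each participant". The control arm has no group format; under Usual Care Control Group (CG): "People assigned to this group will receive no intervention or psychoeducational material".

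The Sample size section says "we estimate that a sample size of 56 participants per group (168 in total) will be sufficient" for a 19-point difference in incidence at α = .05 and power .80. It then moves to about 60 per group for 5-8% attrition. It mentions no ICC, group size or design effect.

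The Statistical analyses section plans:
- for depressive symptoms, "mixed factorial analysis of variance (ANOVA) tests with repeated measures";
- for dropout, a chi-square test;
- for attendance, homework and satisfaction, independent-samples t-tests;
- for the primary outcome, cumulative incidence with relative risk (RR) and number needed to treat (NNT), plus a survival analysis whose model is not named.

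Neither call group nor therapist enters any of these.

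**The concern.** At about 60 per arm and 5 per group, each active arm contains about 12 call groups. Their members share five sessions of 90 minutes, and the interventions include training in assertive communication and in building social contact. Some similarity of outcome within a group is therefore plausible. Controls have no such structure.

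The word 'mixed' in the planned ANOVA does not deal with this. It refers to between- and within-subject factors, so it handles repeated measures on one person but not membership of a shared group.

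Tests that assume independence would then understate the variance in the two active arms. Each active-versus-control comparison has one clustered arm. CBC versus BAC, the dismantling comparison, has two and takes the full design effect. The same holds for attendance, homework and satisfaction when CBC and BAC are compared.

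**Working it through.** **Inputs from the protocol.** 56 per group evaluable and about 60 after attrition; 19-point difference; α = .05 (taken as two-sided); power .80; attrition 5-8%; groups of about 5 in CBC and BAC; no groups in control.

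**Assumptions.** ICC 0.01, 0.05 and 0.10. Base rates are not stated, so 6% versus 25% is used because it returns the planned 56.

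**1. The plan's own figure.** Pooled two-proportion formula, mean rate 0.155:

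n = [1.96·√(2·0.155·0.845) + 0.842·√(0.06·0.94 + 0.25·0.75)]² / 0.19² = [1.003 + 0.416]² / 0.0361 ≈ 56.

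Other formula variants return 56 at nearby rates, so this pair is possible but not established. For attrition, 56/0.95 = 59 and 56/0.92 = 61. Attrition alone takes 56 to about 60, leaving no visible room for clustering.

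**2. Design effect.** DE = 1 + (5 − 1)·ICC. Effective size of a 60-person active arm = 60/DE.

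**3. Type I error of an unadjusted 5% test.**
- Active versus control: SE ratio √((1 + DE)/2).
- CBC versus BAC: SE ratio √DE.
- True α = 2·(1 − Φ(1.96 / SE ratio)).

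| ICC | DE | Effective n of 60 | SE ratio, active v control | True α | SE ratio, CBC v BAC | True α |
|---|---|---|---|---|---|---|
| 0.01 | 1.04 | 58 | 1.010 | 5.2% | 1.020 | 5.5% |
| 0.05 | 1.20 | 50 | 1.049 | 6.2% | 1.095 | 7.4% |
| 0.10 | 1.40 | 43 | 1.095 | 7.4% | 1.183 | 9.8% |

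**4. Power at 56 per group for a correctly adjusted test, 6% versus 25%.** Null SE = √(0.155·0.845·(1 + DE)/56); alternative SE = √((0.0564·DE + 0.1875)/56); power = Φ((0.19 − 1.96·null SE)/alternative SE).
- ICC 0.05: Φ((0.19 − 1.96·0.0717)/0.0675) = 0.768.
- ICC 0.10: Φ((0.19 − 1.96·0.0749)/0.0690) = 0.734.
- Without clustering: 0.802.

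**5. Sensitivity to the base rates.** At 2% versus 21%, the unclustered requirement is 44 per group. Power at 56 is then 0.872 at ICC 0.05, 0.849 at ICC 0.10 and about 0.80 even at ICC 0.20.

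**6. Confidence intervals for incidence if the intervention works.** The clustered arm then has the lower rate and the smaller binomial variance. At 6% versus 25%, the SE ratio is √((0.0564·DE + 0.1875)/0.2439), which gives 1.005, 1.023 and 1.045 at ICC 0.01, 0.05 and 0.10. That is about half the inflation shown in step 3 for active versus control.

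**The case against.** The strongest reply is that the harm is conditional and small where it matters most. A reader might infer three stronger things that the protocol does not support.

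- **That standard errors and p-values are too small as a matter of fact.** They are too small only if the within-group ICC is positive, and no ICC is given.
- **That every analysis assumes independence.** RR and NNT are described only as quantities to be calculated, with no test or standard error fixed. The survival model is unnamed, so a robust or frailty variance is not excluded. Such detail is commonly left to a fuller analysis plan. What the text does fix is the ANOVA on CES-D, a secondary outcome, and the chi-square and t-tests on dropout, adherence and satisfaction.
- **That the trial is underpowered.** With base rates unstated, 56 per group may hold slack, as step 5 shows.

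The central hypothesis is also active versus control, where only one arm is clustered and the distortion is modest. The upper figure of 9.8% needs ICC 0.10 and applies only to CBC versus BAC, a secondary hypothesis. Nor does the protocol say how many therapists there are or how they are allotted to groups, so a therapist effect can be neither asserted nor sized.

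All of this limits the scope and weight of the point. It does not remove it: group delivery is explicit, the sample size shows no allowance for it, and several tests are named that do not fit the design.

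**Conclusion.** The point holds in a conditional form. The design is partially nested, and neither the sample size nor the tests actually named take account of that. For incidence and survival, the protocol is silent on a group term rather than wrong.

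If outcomes correlate within call groups at an assumed ICC of 0.01 to 0.10, nominal 5% tests run at about 5.2-7.4% for active versus control and 5.5-9.8% for CBC versus BAC. The type I error figures rest on the ICC and on groups of 5, not on the base rates. The power figures (about 0.77 and 0.73 at ICC 0.05 and 0.10) also need 6% versus 25%.

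This should be fixed, chiefly for the dismantling comparison. It is not a defect that by itself overturns the central active-versus-control conclusion.

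**What to change.** - Record the call-group ID, and the therapist ID, for every CBC and BAC participant while the sessions are being delivered.
- For CES-D, replace the ANOVA with a mixed model for the repeated measures that has a random call-group effect in the CBC and BAC arms only, with small-sample degrees of freedom (for example Satterthwaite).
- For incidence and survival, use cluster-robust or frailty variance, with each control as a cluster of one.
- Apply the same group adjustment to the CBC versus BAC comparisons of dropout, attendance, homework and satisfaction.
- Beside the 56 per group, state the assumed ICC, the design effect, the base rates and the resulting power. Enrolment need not increase.

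The cost is two ID variables and a model term, slightly wider intervals and a slightly lower stated power. If the ICC proves close to zero, little is lost.

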**Discussion:**

This study will provide evidence of the efficacy of a cognitive-behavioral intervention to prevent depression in caregivers with elevated depressive symptoms administered via conference call, and on the impact of the behavioral activation component on the overall efficacy of the program. If we find favorable results, it would mean that we have developed a program of prevention of depression of higher clinical utility and efficacy than those currently available, which would make it possible for a large number of caregivers to have access to such resources.

**Trial registration:**

ClinicalTrials.gov: NCT02292394. Registered 6 November 2014.

## Background

Across the countries of the Organization for Economic Co-operation and Development (OECD), more than one in ten adults is involved in non-professional, typically unpaid, caregiving, defined as providing help with personal care or basic activities of daily living to people (family or friends) with functional limitations [1]. However, caring for a dependent family member involves emotional consequences for caregivers [2], and can adversely affect their mental health. In fact, it has been found that between 18 % and 48.3 % of caregivers have elevated depressive symptoms [3, 4] and 8.9 % meet the criteria for a major depressive episode [5].

Given their vulnerability, various programs of psychological intervention have been developed for caregivers [6, 7], especially for those with depressive symptoms [8]. However, despite the evidence that having subclinical depressive symptoms is a predictor of developing depression [9], there are only two randomized controlled trials [10, 11] aimed at preventing depression in caregivers with high levels of symptoms that have not yet developed the disorder (i.e., indicated prevention [12]). These interventions achieved a significant reduction in depressive symptoms, but were applied face to face, and face-to-face interventions, pose accessibility barriers to caregivers. Many caregivers cannot participate in face-to-face interventions due to difficulties such as time constraints, lack of financial resources, lack of available and geographically accessible support services, transportation problems, and problems finding a substitute caregiver to the care for the familiar or stigmatization.

To overcome these barriers, communication technologies available to most people in their homes, such as the telephone, can be used to implement the interventions. There is evidence that psychotherapy via telephone for the treatment of depressive symptoms is effective in reducing depressive symptoms compared to control conditions [13]. However, only two studies [14, 15] have evaluated using telephone interventions to reduce depressive symptoms in the caregiver population. They were not indicated prevention interventions for depression, and results revealed that the interventions were partially efficacious in reducing depressive symptoms. Davis and colleagues [14] found no significant differences in depressive symptoms between the face-to-face intervention conducted in home, the phone intervention and the control group. Smith and Toseland [15] only found decreased depressive symptoms in a subsample of caregivers' children. Furthermore, the small sample size, lack of long-term monitoring, the high number of sessions (12 sessions) and interventions that did not follow a theoretical model pose significant limitations that may have contributed to restrict their results.

Moreover, the most effective interventions to reduce depressive symptoms and prevent depression are multicomponent cognitive-behavioral programs [8, 16]. Specifically, in an indicated prevention intervention, Vázquez and colleagues [11] applied cognitive techniques to change thought patterns (e.g., double-standard technique, priming) and behavioral techniques to active behaviors (e.g., pleasant activities planning, reinforcement). They found a significant reduction in the incidence of depression (1.1 % vs. 12.2 %) and depressive symptoms (Cohen's *d* = 1.05) when compared to the control group. Using a dismantling strategy could help identify the contribution of behavioral activation techniques to the therapeutic change. As a result, this can contribute to the improvement of the prevention program and to greater efficiency. The behavioral activation techniques should play an essential role because assuming the caregiver role entails a number of behavioral changes related to leisure and recreation, family life and work that may involve a loss of positive reinforcement and an increase in aversive experiences, factors relevant to the development of depression [17]. In fact, a link between the shortage of leisure activities for caregivers and depressive symptoms has been previously demonstrated [18]. Furthermore, previous research [19–22] comparing antidepressant medication, cognitive techniques aimed at the automatic thoughts and underlying schemes, and behavioral activation techniques have shown that behavioral interventions are sufficient to effectively and efficiently treat depression.

The objectives of the current study are to (a) evaluate the efficacy of a complete cognitive-behavioral intervention (including modification of negative and behavioral activation techniques) and one consisting solely of behavioral activation techniques, both of them administered in a conference call to caregivers with high depressive symptoms; and (b) analyze the mediators of change in depressive symptoms. As the central hypothesis, we expect both interventions to significantly reduce the incidence of depressive episodes and symptoms compared with the control group at post-treatment and at the 1-, 3-, 6- and 12-month follow-up. As secondary hypotheses we expect that (a) the two interventions will differ in the degree of improvement; (b) the change in automatic negative thoughts, self-efficacy will mediate the effect of the complete intervention and the increase in the reinforcement will mediate the effect of the intervention with behavioral component.

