## Methods

### Design

The current study will be a randomized controlled clinical trial, wherein a dismantling design will be used. The dismantling design consisted of analyzing the components of a treatment package by removing one component of therapy in one of the comparison groups [23]. Specifically, three groups will be compared: (a) a cognitive-behavioral intervention via conference call (CBC) with cognitive and behavioral techniques; (b) a behavioral activation intervention via conference call (BAC) with only behavioral techniques aimed at activating behavior; and (c) a control group (CG) in which caregivers receive usual care.

The phases of the study are shown in Fig. 1. There will be six measurement points in the three groups (i.e., pre-treatment, post-treatment and 1-, 3-, 6- and 12-month follow-ups). The first is baseline (pretreatment). Once the caregivers who meet the eligibility criteria are selected and we administer the interventions, we will conduct a post-treatment evaluation and four subsequent follow-ups at 1, 3, 6, and 12 months. To minimize the loss of subjects, we followed the strategies recommended by Grady and colleagues [24] such as excluding those participants likely to drop out; treat participants with kindness, affection and respect or obtain several contact numbers to be able to track the participant down in the future.

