#### Cognitive-Behavioral Intervention via Conference Call (CBC)

CBC is an intervention based on the multifactorial integrative model of depression by Lewinsohn and colleagues [17], which considers depression as the outcome of behavioral, cognitive and emotional changes initiated by the environment and moderated by cognitive factors. The intervention will be adapted from a previous intervention of indicated prevention of depression applied face-to-face in a group format [11]. During the intervention the participants will be trained in various cognitive and behavioral skills such as self-monitoring of mood and activity, relaxation techniques, self-reinforcement, increasing pleasant activities, behavioral contracts, techniques aimed at increasing positive thoughts and decreasing depressogenic ones, training in assertive communication and strategies to increase social contacts.

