#### Behavioral Activation Intervention via Conference Call (BAC)

BAC will also be adapted from the program developed by Vázquez and colleagues [11]. However, the intervention will focus on the behavioral activation component of the intervention. During the intervention the participants will be trained in different behavioral strategies such as self-monitoring of mood and activity, self-reinforcement, increasing pleasant activities, behavioral contracts, and training in assertive communication and in strategies to increase social interactions.

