Moreover, the dismantling design of the current study will allow the identification of the contribution of the behavioral activation component to the efficacy of the complete intervention program. This is a significant development because until now no such analysis has been conducted in any study aimed at caregivers. Similar to the results found in clinical interventions for the treatment of depression [20–22], it is expected that the intervention of indicated prevention of depression with techniques designed for behavioral activation will obtain results similar to those of the full cognitive-behavioral intervention. In the literature, behavioral activation has been considered effective in treating depression in adults [19], and it has been included as an evidence-based treatment for depression in guidelines released by the National Institute for Health and Clinical Excellence [43]. If the effect of behavioral activation is powerful enough, it would offer significant benefits to clinical practice, such as achieving simpler effective interventions for caregivers, which may be attractive to clinicians as they are shorter and easier to learn and apply. In addition, behavioral activation can be administered by non-specialized personnel after brief training.

The strengths of this clinical trial include the specification of the level of prevention and the selection of participants accordingly, *a priori* sample size estimation, randomized, controlled design with allocation concealment, implementation of an intervention based on a theoretical model of depression (which was efficacious in previous clinical research) and applied using a manual, evaluation of adherence to protocol, the evaluation of the results by trained professionals who where blind to the study conditions, and 12 months of follow-up. For the evaluation of the outcome measures we will use validated instruments with sound psychometric properties (see [44]). The incidence of depression as primary outcome will be assessed with the SCID-CV, which has been used as the gold standard for clinical diagnosis [45]. Depressive symptoms as secondary outcomes will be evaluated with the CES-D, which is the most widely used tool to assess depressive symptoms in the population of caregivers [46]. In addition, the study will be conducted in the community context where the caregivers live, resulting in a high level of generalizability.

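### The article predicts both that CBC and BAC will differ and that they will be similar, and it sets no difference or margin against which a non-significant CBC–BAC result could support similarity

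*Protocol article*

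**What the plan says.** All references are to the protocol article.

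- **Background (objectives and hypotheses).** The central hypothesis is that both interventions beat control. Secondary hypothesis (a) is that "the two interventions will differ in the degree of improvement", with no direction, size or named outcome.
- **Discussion.** Behavioural activation alone is expected to be a match for the complete programme: it "will obtain results similar to those of the full cognitive-behavioral intervention". The same paragraph says the design will identify what behavioural activation contributes, and describes conditional benefits for practice, among them simpler and shorter interventions.
- **Sample size.** The calculation is that "a sample size of 56 participants per group (168 in total) will be sufficient to detect a difference of 19" per cent in the "rates of incidence of depression episodes between experimental and control conditions", "assuming α = .05 and a power (1 - β) of .80". No CBC–BAC quantity is given.
- **Design.** Dismantling is defined as "analyzing the components of a treatment package by removing one component of therapy in one of the comparison groups".
- **Intervention sections.** CBC includes "self-monitoring of mood and activity, relaxation techniques, self-reinforcement, increasing pleasant activities, behavioral contracts", followed by thought-modification, assertiveness and social-contact techniques. BAC includes "self-monitoring of mood and activity, self-reinforcement, increasing pleasant activities, behavioral contracts, and training in assertive communication" and social-contact strategies. Relaxation and thought modification appear only under CBC.
- **Interventions (general).** Each programme has five weekly 90-minute sessions.

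**The concern.** The two statements concern the same contrast and cannot both be the trial's expectation. A significant difference would agree with the Background and a non-significant one could be taken to agree with the Discussion, so almost any result has a prediction to confirm. The second case matters more. Failing to reject equality is not evidence of similarity unless the interval is narrow relative to a margin, and the article states none. At stake is whether the trial may say that behavioural activation alone does as well as the full programme, which is the conclusion to which the Discussion attaches its practical benefits.

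A smaller issue affects what the contrast means. If relaxation is left out of BAC along with the cognitive techniques, CBC minus BAC is the effect of both together, and the Design section's statement that one component is removed does not describe it.

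**Working it through.** **1. The stated sample size.** The inputs are a 19-point difference, α = 0.05 (two-sided assumed) and power 0.80. No base rate is given, so n is not fixed: across base rates the two-sided figure runs from 37 to 108 per arm. An assumed 6 % versus 25 % recovers the stated number:

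n = [1.96·√(2·0.155·0.845) + 0.8416·√(0.06·0.94 + 0.25·0.75)]² / 0.19² = (1.003 + 0.416)² / 0.0361 ≈ 55.8, so 56.

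With attrition, 56/0.95 gives 59 and 56/0.92 gives 61, in line with about 60. The figure is attainable, and it relates to intervention versus control.

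**2. CBC versus BAC on incidence.** The rates below are assumptions, because the article gives none for this contrast. The nearest figures are those of the earlier face-to-face trial quoted in the Background: 1.1 % versus 12.2 %, a difference of 11.1 points.

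95 % half-width with 60 per arm, equal rates p, is 1.96·√(2p(1−p)/60):

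| Assumed p in both arms | Half-width (points) |
|---|---|
| 1.1 % | 3.7 (under one expected event per arm; poor approximation) |
| 5 % | 7.8 |
| 10 % | 10.7 |

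Power for a difference:
- 1.1 % versus 6.1 %, 60 per arm: exact power of the uncorrected chi-square test is 0.29, so the result is non-significant about 71 % of the time. The 5-point gap is 5/11.1 = 45 % of the earlier trial's effect.
- 6 % versus 15.5 % (half of the 19 points lost): power 0.37 with 56 per arm and 0.39 with 60.
- 6 % versus 25 % (BAC no better than control): power 0.80 with 56 per arm.

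Showing non-inferiority (one-sided 0.025), n = (1.96 + 0.8416)²·2p(1−p)/margin²:
- p = 6 %, margin 9.5 points: 7.849·0.1128/0.009025 ≈ 98.1, so 99 per arm; power with 56 is 0.56.
- p = 1.1 %, margin 5.55 points: nominally 56 per arm, but only 56·0.011 = 0.6 expected events per arm.

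**3. CBC versus BAC on CES-D (SD units, 60 per arm).**
- One unadjusted time point: 1.96·√(2/60) = 0.36 SD; power for a 0.3 SD difference is about 0.37.
- Baseline-adjusted mean of the five later assessments, common correlation ρ assumed: variance factor (1 + 4ρ)/5 − ρ². At ρ = 0.5 this is 0.60 − 0.25 = 0.35, half-width 1.96·√(2·0.35/60) = 0.21. At ρ = 0.7 it is 0.76 − 0.49 = 0.27, half-width 0.19. Power for a sustained 0.3 SD difference is about 0.79 and 0.89.

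**4. Content of the arms.** Set side by side, the two lists share self-monitoring, self-reinforcement, pleasant activities, behavioural contracts, assertive communication and social contacts. CBC alone has thought modification and relaxation, so as printed two items are removed and not one.

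**The case against.** The strongest reply has four parts.

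*The contrast is secondary.* A trial need not be powered for a secondary hypothesis, and the Sample size section is open about what was sized. This stands: the lack of power is not itself an error. A reader might infer that the trial cannot answer its dismantling question at all. The article does not support that. CBC–BAC can be estimated, a very large difference is detectable, and BAC versus control tests directly whether behavioural techniques alone work.

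*No passage plans to infer equivalence from a non-significant test.* True. The Discussion states an expectation and then speaks conditionally, and a margin may exist in a fuller protocol or analysis plan. Its absence from a condensed article is not the fault. The fault is that two opposed expectations are printed with nothing to decide between them.

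*The technique lists are examples.* Both are introduced as such, and the manuals were still to be written. It is therefore not established that relaxation is withheld from BAC, only that the wording needs reconciling. Likewise, that BAC gives each technique more time is inference, since nothing allocates time within sessions. Equal contact time is a defensible choice.

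*The magnitudes are not those of the planned analysis.* Partly right. Dropouts count as depressive episodes, so analysed rates would exceed the raw ones, and repeated CES-D measurements can make that comparison much more precise than a single time point. The planned repeated-measures ANOVA may also differ from the adjusted mean used above. The CES-D result is therefore a range, and a blanket statement that CES-D is imprecise would be wrong.

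**Conclusion.** The contradiction between the Background and the Discussion is real and is printed in current text. Since the article sizes only intervention versus control and states no CBC–BAC difference or margin, a non-significant CBC–BAC result could not support the expected similarity. On incidence, a moderate loss of benefit would often go undetected: about 71 % of the time at an assumed 1.1 % versus 6.1 %, with a half-width of about 7.8 points at an assumed 5 %. These figures rest on assumed rates and 60 analysed per arm. On CES-D the half-width lies between about 0.36 SD and about 0.2 SD, depending on the analysis and on a correlation that the article does not give.

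It would be too strong to say that every margin is out of reach, because at very low incidence a margin of about 5.5 points is nominally attainable. The relaxation discrepancy is a matter of wording to be reconciled. The point should be acted on, because it changes what the trial may conclude.

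**What to change.** 1. State one secondary objective for CBC versus BAC, identical in the Background and the Discussion: a two-sided estimate with 95 % confidence interval for incidence and for CES-D.
2. Allow a claim of similarity only if that interval lies wholly within a margin fixed in advance and justified, for instance as a stated fraction of the earlier trial's effect. Otherwise call the result inconclusive.
3. Use BAC versus control for the question whether behavioural activation alone works.
4. Reconcile the Design, CBC and BAC sections on relaxation. If the contents stay as listed, describe the contrast as cognitive plus relaxation techniques.
5. Do not present a shorter intervention as a conclusion of this trial, since both programmes have the same number and length of sessions.

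The cost is wording and agreement on a margin; no participants or visits are added. The downside is a more modest claim about CBC versus BAC, and quite possibly an inconclusive one on incidence.
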